## Abstract

**Background:**

Knee osteoarthritis (OA) is a common and important cause of pain and disability, but interventions aimed at modifying structures visible on imaging have been disappointing. While OA affects the whole joint, synovitis and effusion have been recognised as having a role in the pathogenesis of OA. Krill oil reduces knee pain and systemic inflammation and could be used for targeting inflammatory mechanisms of OA.

**Methods/design:**

We will recruit 260 patients with clinical knee OA, significant knee pain and effusion-synovitis present on MRI in five Australian cities (Hobart, Melbourne, Sydney, Adelaide and Perth). These patients will be randomly allocated to the two arms of the study, receiving 2 g/day krill oil or inert placebo daily for 6 months. MRI of the study knee will be performed at screening and after 6 months. Knee symptoms, function and MRI structural abnormalities will be assessed using validated methods. Safety data will be recorded. Primary outcomes are absolute change in knee pain (assessed by visual analog score) and change in size of knee effusion-synovitis over 24 weeks. Secondary outcomes include improvement in knee pain over 4, 8, 12, 16 and 20 weeks. The primary analyses will be intention-to-treat analyses of primary and secondary outcomes. Per protocol analyses adjusting for missing data and for treatment compliance will be performed as the secondary analyses.

**Discussion:**

This study will provide high-quality evidence to assess whether krill oil 2 g/day reduces pain and effusion-synovitis size in older adults with clinical knee OA and knee effusion-synovitis. If krill oil is effective and confirmed to be safe, we will provide compelling evidence that krill oil improves pain and function, changes disease trajectory and slows disease progression in OA. Given the lack of *approved therapies* for slowing disease progression in OA, and moderate cost of krill oil, these findings will be readily translated into clinical practice.

**Trial registration:**

Australian New Zealand Clinical Trials Registry, ACTRN12616000726459. Registered on 02 June 2016.

Universal Trial Number (UTN) U1111–1181-7087.

## Background

Osteoarthritis (OA) is a major cause of pain, functional limitation and disability worldwide [1], with hip and knee OA ranked as the 11th highest contributor to global disability and 38th highest in disability-adjusted life years (DALYs) [2]. Treatment remains focussed on managing pain, which is ranked by patients as the highest treatment priority [3]. However, pain control remains poor in 50% of non-operatively treated patients [4]. Despite the large disease burden, currently no approved disease modifying OA drugs (DMOADs) are available.

OA is a heterogeneous, complex disease with multiple phenotypes [5, 6]. Few treatments have been demonstrated to be effective for OA pain and to slow down changes in structure, and this may be partly due to treating everyone as if they have the same pathological process. Treatment can be optimised by selecting study populations by subgroups with specific features that are likely to respond to targeted treatments. One such phenotype is an inflammatory phenotype.

OA is typically considered a ‘non-inflammatory’ type of arthritis; however, localised low-grade inflammation is an important factor in OA pathogenesis, with inflammatory patterns observed both early [7] and late [8] in the disease process. In OA, inflammatory changes have been demonstrated both systemically and in the affected joint. Moreover, there is now evidence that inflammation helps distinguish clinically distinct phenotypes of OA [9].

Elevated levels of systemic inflammation (as observed by high sensitive C reactive protein (hsCRP) [10] are observed in persons with OA compared to controls, and are positively correlated with the degree of synovial inflammatory infiltration in OA [11]. hsCRP levels are associated with both symptoms and disease markers, with higher hsCRP levels associated with greater pain (in both a meta-analysis [10] and longitudinal data from our centre [12]), decreased physical function [10], decreased cartilage volume [13] and disease progression [7, 14]. Therefore, systemic inflammation predicts both pain and structural outcomes in OA.

Inflammation also occurs locally within joints. Pro-inflammatory cytokines, including interleukin (IL)-1β, tumour necrosis factor-α (TNF-α), and IL-6 are produced by synovium and chondrocytes, and contribute to the progression of cartilage degradation [8]. Localised inflammation presents as effusion (excess synovial fluid within the joint space) and/or synovitis (thickening of the synovium); these predict pain [15–18], including new and worsening pain over 2.6 years [18]. Effusion-synovitis also predicts structural changes— cartilage defects, bone marrow lesions (BMLs) and increased cartilage loss over 2.6 years [19]—and joint replacement [20]. Thus, stopping the cascade of inflammation is likely to slow down deleterious changes in knee structure and reversing inflammation has the potential to improve outcomes globally in knee OA.

High levels of inflammation in OA can be targeted with treatments including oral prednisolone [21] or biologics [22], but these therapies are expensive and have too many side effects for widespread use. Safer treatments for reducing inflammation are needed.

Fish oil is effective in people with rheumatoid arthritis (RA), reducing pain [23], morning stiffness and number of painful and/or tender joints [23, 24], and non-steroidal anti-inflammatory drug (NSAID) consumption [23, 25]. This is an effective add-on therapy to standard RA therapies, reducing the risk of treatment failure and increasing the rate of remission [26]. Efficacy data on the use of marine-sourced oils is more limited in people with OA. Observational data suggest that omega-6 and omega3 polyunsaturated fatty acids from dietary sources may have beneficial effects on synovitis and cartilage damage cross-sectionally [27], but that use of a variety of marine oils is ineffective for OA pain [28, 29], although there is marked heterogeneity amongst the predominantly poor quality trials [28], and none were enriched for participants with evidence of an inflammatory phenotype. Canola oil/low dose fish oil may be effective [29]. However, unlike marine oils in general, oil from Antarctic krill (*Ephausia superba*, a zooplankton crustacean) may be effective in people with OA. Like fish oil, it is high in eicosapentanoic acids (EPA) and decosahexanoic acid (DHA) [30], although the chemical structures of the fatty acids differ (phospholipids, rather than triacylglycerol or fatty acid ethyl esters); but unlike fish oil, it also naturally contains antioxidants (predominantly astaxanthin [30]). Additionally, bioavailability of krill oil is better than fish oil, as comparable amounts of EPA and DHA are obtained from lower doses of krill oil compared to fish oil [31]. In animal studies, krill oil supplementation had larger effects on most clinical outcomes than fish oil [32], while krill oil reduced the severity of inflammatory arthritis in mice by 50% compared to controls [32]. In mice transgenic for human TNF-α, both fish and krill oil improved plasma cholesterol levels, but only krill oil had additional beneficial effects on markers of fatty acid oxidation [33]. Therefore, bioavailability data and animal studies suggest that krill oil has anti-inflammatory and anti-oxidative effects and may be a better treatment in vivo than fish oil.

Two randomised controlled trials (RCTs) including people with osteoarthritis have demonstrated that daily krill oil (300 mg [34] or 2 g [35]) is effective in reducing some aspect of knee pain [34, 35], functional impairment [34, 35], and stiffness [35]. However, these RCTs have methodological limitations, including being of short duration (30 days), having poor documentation of adverse events, not including any imaging data to determine the effect of krill oil on knee structures, and not targeting patients with evidence of inflammation.

Therefore, we aim to compare, using a randomised, placebo-controlled double-blind design over 6 months, the effect of 2 g krill oil daily compared to identical placebo, on knee pain and MRI-detected knee effusion-synovitis size (primary outcomes) in participants with clinical knee OA, significant knee pain and effusion-synovitis on MR imaging over 24 weeks.

## Objective

We are conducting a multi-centre randomised, placebo-controlled double-blind clinical trial. This will compare efficacy of krill oil vs identical placebo to treat knee OA (both pain and structure) in 260 patients with clinical knee OA, significant knee pain and effusion-synovitis on imaging.

We hypothesise that krill oil (2 g daily) will decrease pain (assessed by 100 mm visual analog scale (VAS)) score by 10 mm more than identical placebo over 24 weeks and decrease effusion-synovitis size over 24 weeks (co-primary hypotheses) and improve knee pain over 4, 8, 12, 16, and 20 weeks (secondary hypotheses) in patients with symptomatic knee OA and knee effusion-synovitis, compared with placebo. If krill oil proves effective, it will offer a novel therapeutic approach to reduce knee OA progression.

## Methods/design

### Study design

This randomised trial of krill oil for OA of the knee (KARAOKE) study is a multicentre, randomised, double-blind, placebo-controlled superiority trial over 24 weeks. The trial was registered on the Australian New Zealand Clinical Trials Registry prior to recruitment, and trial reporting will be guided by the Consolidated Standards of Reporting Trials (CONSORT) statement [36]. We aim to recruit a convenience sample of 260 patients with clinical knee OA, significant knee pain and effusion-synovitis visualised on MRI. Patients will be recruited via the OA Clinical Trial Network, at Australian public hospitals in Melbourne, Sydney, Adelaide and Perth and a research institute in Hobart, using a combined strategy, including collaboration with general practitioners, rheumatologists and orthopaedic surgeons, as well as advertising through local and social media. Patients will be encouraged to contact their local research nurse via email or telephone.

### Inclusion criteria

Inclusion criteria are as follows: males and females aged ≥ 40 years; with significant knee pain on most days (defined as a pain score ≥ 40 mm on a 100-mm VAS); and meeting the American College of Rheumatology (ACR) criteria for symptomatic knee OA [37], assessed by a physician, and any effusion-synovitis present on MRI (defined as grade 1 or more according to modified WORMS scoring [18, 38]).

### Exclusion criteria

Exclusion criteria are as follows:
Significant knee injury within the last 6 monthsUse of anticoagulants, high dose aspirin or NSAIDs, as krill oil is contraindicated in such peopleUnwillingness to stop taking krill oil and fish oil medications 30 days prior to the trial and during the trial (minimum washout 4 weeks)Other forms of inflammatory arthritis (especially rheumatoid arthritis and gout)Seafood allergyArthroscopy or open surgery in the “study” knee in the last 12 monthsInjections of corticosteroids (last 3 months) or hyaluronic acid (last 6 months) in the index kneeWomen who are pregnant or breastfeedingUse of any investigational drug(s) and/or devices within 30 days prior to randomisationPresence of any serious medical illness that may preclude 24-week follow-upInability to provide informed consentInability to have an MRI (claustrophobia, pacemakers, metal in eyes, metal in knees that disrupt the images at the area of interest)Severe knee OA (joint space narrowing (JSN)) on x-ray of grade 3 using the Osteoarthritis Research Society International (OARSI) atlas [39])

### Randomisation and blinding

Study participants were allocated to receive either krill oil or placebo in a 1:1 ratio based on computer-generated random numbers using a central randomisation website hosted by the University of Tasmania using adaptive allocation (minimisation) [40]. Briefly, the randomisation program examined the number of participants that were currently assigned to each of the two arms and then adjusted the randomisation thresholds so that the arm with the fewest participants would have a greater chance of being selected. Randomisation will be stratified by study site and is accessible by a dedicated website. This will be conducted by staff members with no direct involvement in the study.

The randomised controlled trial will be a double-blind one, with both patients and investigators assessing outcomes blinded to treatment allocation. Allocation concealment and double blinding will be ensured by: 1) use of identical softgels for each group; 2) objective measures of knee structural changes being made by trained observers blinded to group allocation; and 3) subjective measures being taken by research nurses blinded to group allocation.

Emergency unblinding will be allowed in limited situations that impact on the safety of study patients. Code-break for the full randomisation schedule will be maintained by the University of Tasmania. Patients who are unblinded will be withdrawn from treatment but will continue to be followed as per the planned follow-up schedule.

### Intervention

Eligible people will receive 2 × 1 g softgels daily of either krill oil or placebo for 6 months. The krill oil (Superba Boost product) contains 190 mg/g of EPA and 100 mg/g of DHA. The total omega-3 content is 350 mg/g, total omega-6 is 12 mg/g, hence the omega-3 to omega-6 ratio is 29. The placebo used is a mixture of vegetable oils (virgin cold pressed olive oil, maize oil, palm kernel oil, medium chain triglycerides), containing no EPA or DHA, and less than 5 mg/g (0.5%) other omega-3s (predominantly oleic acid (C18:1n9) and linoleic acid (C18:2n6)). Both the krill oil and the placebo are provided in non-distinguishable opaque glycerin softgels. A small amount of vanilla flavour added to the shell of both active and placebo softgels to ensure uniform taste and smell. All patients will continue usual care by their treating health practitioners.

### Study procedure and time points

Research assistants will first conduct screening over the telephone. If early checks of study eligibility are favourable, participants will be booked in for a face-to-face screening visit to further determine eligibility and explain what is involved in the study. At the screening face-to-face visit, patients will complete questionnaires, have a knee x-ray and MRI, supply a blood sample and have a clinical assessment by a study doctor to ensure inclusion criteria are met. The study knee will be defined as the one with symptomatic OA meeting all inclusion criteria. If both knees meet these criteria, the study doctor will decide which is the study knee, typically the one with the highest pain score.

Table 1 outlines the schedule of assessments. After screening, there will be three study visits (weeks 0, 12 and 24). The same research assistants, who are blinded to treatment allocation, will measure all clinical variables, administer questionnaires, monitor compliance and record adverse events at these visits. Additional questionnaire mail outs will occur monthly. MRI scans will occur at screening and week 24; knee x-ray will be performed at screening; blood samples are taken at screening, 12 and 24 weeks, and urine samples are taken at baseline and week 24.

**Table 1 Tab1:** Schedule of assessments, KARAOKE study

Visit/week number	Screening	Baseline (week 0)	4	8	12	16	20	24
Informed consent	x							
Knee x-ray	x							
Knee MRI	x*							x
Clinical measures								
Bloods	x				x			x
Clinical examination	x							
Leg strength		x			x			x
Height and weight		x						x
Capsules given		x			x			
Capsule count					x			x
Pressure pain testing (Melbourne/Perth only)		x			x			x
Ultrasound (Perth)		x						x
Questionnaire measures								
Knee VAS	x	x	x	x	x	x	x	x
Knee WOMAC		x	x	x	x	x	x	x
Knee ICOAP		x	x	x	x	x	x	x
Patient global evaluation		x	x	x	x	x	x	x
Joint replacement surgery	x				x			x
Concomitant medications	x				x			x
Safety (AEs)					x			x
Hand VAS, back VAS		x	x	x	x	x	x	x
AQoL		x			x			x
Patient health questionnaire (PHQ-9)		x						
Pain at other sites		x			x			x
Treatment guessing					x			x
painDETECT		x						
Adverse events	As required							
Early withdrawal	As required							

*if otherwise suitable

Participants will discontinue involvement in the study if they need to use drugs that are contraindicated (marine oils, anticoagulants, high dose aspirin, NSAIDs), they stop taking study medication or the participant or the site investigators request discontinuation.

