#### Concomitant medication

Use of pain medicines will be recorded by questionnaire at all visits. Participants will be asked to keep medications as stable as possible (including NSAIDs) and use paracetamol as rescue medication. Use of fish and krill oil during the trial will not be permitted, and use must cease 2 weeks prior to randomisation. Participants who commence anti-coagulant therapy will be withdrawn from the trial. We will assess analgesic use from the medication data.

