### Statistical analysis

The primary analyses will be intention-to-treat analyses of primary and secondary outcomes. Per protocol analyses will be performed as the secondary analyses.

Changes in knee pain, knee effusion-synovitis size and any other outcomes which were collected using a linear scale will be analysed using a linear mixed model with treatment, month and their interaction (treatment × month) as covariates, as well as outcome measured at baseline and the baseline interaction with month. Incidence of adverse events will be assessed using log binomial regression. Correlated data within trial centres and the repeated measures will be addressed using trial centre and patient identification as random intercepts. Month will be treated as random effect to allow different treatment effects among patients over time. The sensitivity of models to the structure for the random effects and covariance structures will be assessed using likelihood ratio tests. Change in outcome measures within each group and differences in changes between groups from baseline to follow-up will be calculated using linear combinations of the estimated coefficients. If there are baseline imbalances in covariates between treatment groups, we will consider adjusting for them based on whether we regard the imbalance as clinically significant. Missing data caused by loss to follow-up and non-responses will be addressed by adding variables that have complete data at baseline and can explain missingness to the regression models.

Secondary analysis for missing data will be performed in people with full medication adherence (e.g., > 80% of softgels) and using imputation. Baseline variables with complete data will be used for data imputation assuming missing at random.

Subgroup analyses will be performed to examine which subgroups may respond better to treatment. These will include effusion size, radiographic knee OA, co-pathology present on MRI, pain characteristics, levels of inflammatory markers and serum lipid measures. Statistical significance will be set as a two-sided *P* value < 0.05.

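### Stopping study medication or needing a listed drug ends follow-up, so the intention-to-treat analysis would lack outcomes after discontinuation, most seriously for the MRI co-primary outcome

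*Protocol article*

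**What the plan says.** All references are to the protocol article.

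- **Study procedure and time points**, last paragraph: "Participants will discontinue involvement in the study if they need to use drugs that are contraindicated". The list in brackets names marine oils, anticoagulants, high-dose aspirin and NSAIDs. The same sentence adds the cases where "they stop taking study medication or the participant or the site investigators request discontinuation".
- **Concomitant medication**: "Participants who commence anti-coagulant therapy will be withdrawn from the trial". The same section also says: "Participants will be asked to keep medications as stable as possible (including NSAIDs) and use paracetamol as rescue medication".
- **Exclusion criteria**: NSAID use is listed among the reasons not to enrol.
- **Randomisation and blinding**: "Patients who are unblinded will be withdrawn from treatment but will continue to be followed as per the planned follow-up schedule".
- **Withdrawal**: the reason and date are recorded. An early MRI is a possibility for people who cannot attend the last visit, not a commitment.
- **Statistical analysis**: "The primary analyses will be intention-to-treat analyses of primary and secondary outcomes". On missing values: "Missing data caused by loss to follow-up and non-responses will be addressed by adding variables that have complete data at baseline". A secondary analysis imputes from baseline variables under missing at random.

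**The concern.** An intention-to-treat comparison asks what happens to everyone assigned to krill oil against everyone assigned to placebo, whatever they go on to take. It needs outcomes from people who stop the softgels or start another drug. The discontinuation rule removes those people from the study when that happens, so their later outcomes are not observed and the model must supply them.

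In a pain trial some of these exits may be related to outcome. Starting an NSAID, or stopping capsules that do not seem to help, can be a response to knee pain, which is a co-primary outcome. If so, baseline variables alone may not explain who is missing. At stake are the 24-week VAS difference, powered at 10 mm, and the effusion-synovitis difference, powered at 4.5 ml.

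**Working it through.** **1. The rules side by side**

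| Event | Treatment | Follow-up |
|---|---|---|
| Stops study medication | stops | ends |
| Needs a listed drug | stops | ends |
| Starts an anticoagulant | stops | ends |
| Is unblinded | stops | continues |

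The last row shows that the authors separate treatment from follow-up when they mean to. No section extends that to the other three rows.

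**2. What is observed for a leaver**

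Table 1 schedules the knee VAS at weeks 0, 4, 8, 12, 16, 20 and 24, so a leaver contributes every score up to leaving. MRI is scheduled only at screening and week 24. A leaver without an early MRI has no post-baseline effusion-synovitis value, and only baseline variables can support missing at random.

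**3. VAS: size of the bias**

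The documents give no leaving rates, so this is an illustration by simulation with 200,000 participants per setting. Inputs from Sample size calculations are a 10 mm benefit, a placebo change of -15.5 mm and an SD of change of 25.5 mm (built as √(18² + 18²) = 25.5). Assumptions are a baseline mean of 60 mm (SD 12), a linear benefit over time, and leaving when pain crosses a threshold. Scores are not truncated at 100 mm; the threshold (90 to 115) only sets the leaving rate. The effect with full follow-up varies around 10 mm by chance, so comparisons are within a row. Selected rows:

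| Leaving depends on | Leave, placebo / krill oil | Full follow-up (mm) | Completers, baseline-adjusted (loss) | Repeated measures (loss) |
|---|---|---|---|---|
| last recorded VAS | 2.6% / 1.6% | 9.90 | 9.65 (0.25) | 9.88 (0.02) |
| last recorded VAS | 10.6% / 7.5% | 9.84 | 9.19 (0.65) | 9.84 (0.00) |
| last recorded VAS | 22.0% / 16.7% | 9.97 | 8.82 (1.15) | 9.89 (0.08) |
| unrecorded current pain | 2.9% / 1.7% | 9.97 | 9.56 (0.41) | 9.68 (0.29) |
| unrecorded current pain | 11.5% / 7.9% | 9.67 | 8.71 (0.96) | 8.87 (0.80) |
| unrecorded current pain | 23.4% / 16.9% | 9.91 | 8.26 (1.65) | 8.39 (1.52) |

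When leaving depends on recorded pain, the repeated-measures analysis is within about 0.1 mm of full follow-up. When it depends on unrecorded pain, it loses about 0.3-1.5 mm. In all these scenarios the bias shrinks the effect. The simulated analysis has an unstructured covariance; the planned model with random intercepts and random month was not itself simulated.

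**4. MRI: size of the bias**

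Let p be the share leaving in each arm and g the amount by which leavers' true week-24 volume exceeds what baseline variables predict. Then bias = p(placebo) × g(placebo) - p(krill oil) × g(krill oil). With a common g this is the difference in leaving rates times g. Purely as an illustration, a 10-point difference and g as large as the 4.5 ml target give 0.10 × 4.5 = 0.45 ml. With equal rates and equal g it is 0. No intermediate scan can reduce g.

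**5. Power**

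The plan's dropout step reproduces: 234 / 0.90 = 260. On its stated inputs (SD 25.5 mm, 10 mm, two-sided 0.05), 234 evaluable participants give 85.1% power, not 90%. Losses of 15%, 20% and 25% give 83.0%, 80.7% and 78.2%. Extra loss beyond the planned 10% therefore costs about 2.1, 4.4 and 6.9 points. For effusion-synovitis (SD 10.7 ml, 4.5 ml), power is 89.6% at 10% loss and 87.8%, 85.8% and 83.6% at 15%, 20% and 25%.

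**The case against.** The strongest reply is that the intention-to-treat analysis remains feasible. All randomised participants can be analysed as allocated, the mixed model uses each VAS score recorded before leaving, and Withdrawal and the early-withdrawal row of Table 1 give some provision for leavers. This is right about feasibility. It does not supply outcomes after discontinuation, and it does not help the MRI outcome unless the early scan is actually done.

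A second reply is that the discontinuation sentence is loosely worded and means treatment only. Concomitant medication speaks against that, since it withdraws anticoagulant starters from the trial, as does the explicit distinction made for unblinded patients.

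Several stronger readings are tempting, but the documents do not support them:

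- **That intention-to-treat cannot be done, or that no model can recover the effect.** If leaving depends on recorded pain, a suitable repeated-measures model recovers it almost fully.
- **That the primary set becomes an on-treatment set.** The rule covers people who stop, not those who take capsules irregularly. The separate analysis of people taking more than 80% of softgels implies that lower adherers stay in the primary set.
- **That dropout is driven by pain and differs by arm.** This is plausible for NSAIDs and for stopping through lack of effect, but not obviously for anticoagulants or marine oils. No rates are given. How far NSAID use triggers exit is itself unclear, because Exclusion criteria and the discontinuation rule treat it as disqualifying while Concomitant medication asks that it be kept stable.
- **That extra loss pulls VAS power down from 90% to about 80%.** Most of the gap at 15% or 20% loss comes from the sample-size inputs, which give about 85% at the planned loss.

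**Conclusion.** The conflict is certain. One section ends follow-up when treatment stops, another keeps a group in follow-up after treatment stops, and a third declares an intention-to-treat primary analysis that needs those outcomes. The consequence, if the rule is followed as written, is missing post-discontinuation data and reliance on missing at random with mainly baseline variables.

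The size is uncertain. For VAS it ranges from negligible, if leaving depends on recorded pain, to perhaps 0.3-1.5 mm of 10 mm, if it depends on unrecorded pain. This assumes about 3-23% leaving on placebo and 2-17% on krill oil; in these scenarios the benefit is understated. For effusion-synovitis the document gives nothing from which to bound the bias, and no intermediate measurement limits it. The point deserves correction because data not collected cannot be restored by an analysis plan. It does not show that the trial's comparison is invalid.

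**What to change.** 1. Reconcile Exclusion criteria, Randomisation and blinding, Study procedure and time points, Concomitant medication, Withdrawal and Statistical analysis, so that stopping study treatment and leaving follow-up are separate events. The conflicting statements on NSAIDs need reconciling at the same time. No position is taken here on which drugs should lead to stopping treatment.
2. For anyone who stops treatment, for whatever reason, continue the scheduled VAS questionnaires and the week-12 and week-24 visits, including the week-24 MRI, unless consent is withdrawn. Include these data in the intention-to-treat analysis.
3. Trial status reports recruitment complete in July 2019, so new wording helps only people still in follow-up. For participants already withdrawn, report numbers by arm and reason (the reason is already recorded), and state how many had an early MRI.
4. Add a sensitivity analysis for both co-primary outcomes that departs from missing at random, for example by shifting imputed week-24 values for leavers over a stated range in each arm.

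The cost is wording, a small amount of follow-up using assessments already in Table 1, and one further analysis.
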